### Grouping and Intervention

#### Control Group

Clinical respiratory physicians will formulate standardized medication regimens for participants based on the 2023 GOLD guidelines [35] and *Chronic Obstructive Pulmonary Disease: Diagnosis and Management* by American Family Physician [36]. Participants will receive conventional pharmacological treatment throughout this trial. During this study, participants will be instructed to abstain from any form of regular traditional Chinese health-preserving exercises, defined as twice daily sessions of 30 minutes each, five times per week, according to a previous study [39]. To minimize potential attention and contact bias arising from differences in interaction frequency between groups, participants in the control group will attend the hospital once weekly, where this study’s team will manage musculoskeletal conditions unrelated to respiratory function (eg, neck, shoulder, low back, and lower limb pain). Meanwhile, we will restrict our interventions as follows: pain treatment will be limited to symptomatic management of common musculoskeletal issues, without any intervention aimed at improving exercise capacity, and analgesics will not be used. This arrangement is intended to ensure comparable clinical contact time and follow-up support between groups. In addition, the control group will receive at least five telephone follow-ups per week to record medication adherence, daily activity levels, and general health status. No respiratory exercise instruction or respiratory rehabilitation-related intervention will be provided during these contacts. In accordance with ethical considerations, participants in the control group will be offered free Liuzijue exercise guidance after completion of this trial.

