**Methods:**

This study adopts a randomized controlled trial design, with participants randomly assigned to either a control group or a Liuzijue group. The control group receives standardized pharmacological treatment, while the Liuzijue group receives the same pharmacological treatment combined with Liuzijue intervention. The coprimary outcome measures are the 6-minute walk test and surface electromyography of the respiratory muscles. Secondary outcome measures include pulmonary function tests and respiratory questionnaires. Exploratory outcome measures include isokinetic strength testing of the core muscle groups and kinematic analysis.

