**Figure 1. F1:**
[figure not shown]
Flowchart of this trial's design and participant timeline. Eligible patients with stable COPD (GOLD stage II-III) were randomly allocated (1:1) to receive standardized pharmacological treatment alone or combined with a 12-week Liuzijue exercise intervention. Outcomes were assessed at baseline and post intervention, including 6MWT, sEMG, PFT, SGRQ, IKMT, and kinematic analysis. 6MWT: 6-minute walk test; COPD: chronic obstructive pulmonary disease; GOLD: Global Initiative for Chronic Obstructive Lung Disease; IKMT: isokinetic muscle strength test; PFT: pulmonary function test; sEMG: surface electromyography; SGRQ: St. George’s Respiratory Questionnaire.

**Table 1. T1:** Schedule of enrollment, interventions, and assessments according to the SPIRIT^a^ guidelines.

Study period	Baseline	Allocation	Intervention	Assessment
Time point (week)	-2	0	1‐12	13
Enrollment				
Eligibility screen	✓			
Informed consent	✓			
Demographics	✓			
Disease history	✓			
Combination medication	✓			
Centralized guidance	✓			
Phone follow-up	✓	✓	✓	✓
Randomization and allocation		✓		
Interventions				
Control group			✓	
Liuzijue group			✓	
Assessments				
PFT^b^		✓		✓
6MWT^c^		✓		✓
SGRQ^d^		✓		✓
sEMG^e^		✓		✓
IKMT^f^		✓		✓
Kinematics test		✓		✓
Risk management				
Safety assessment			✓	✓
Safety monitoring			✓	✓
Risk prevention			✓	✓
Adverse event reporting			✓	✓

a SPIRIT: Standard Protocol Items: Recommendations for Interventional Trials.

b PFT: pulmonary function test.

c 6MWT: 6-minute walk test.

d SGRQ: St. George’s Respiratory Questionnaire.

e sEMG: surface electromyography.

f IKMT: isokinetic muscle strength test.

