#### Inclusion and Exclusion Criteria

Participants will be screened according to the predefined eligibility criteria before enrollment. Detailed inclusion and exclusion criteria are presented in Textbox 1.

Textbox 1.Inclusion and exclusion criteria for participant eligibility.Inclusion criteriaDiagnosed with stage II moderate chronic obstructive pulmonary disease (COPD) and stage III severe COPD.Maintained a stable condition for at least 12 weeks before randomization, with symptoms of cough, sputum production, and dyspnea remaining stable or mild, and no acute exacerbations occurring during this period.No gender restrictions; aged between 40 and 80 years.Participants who are willing to participate in this trial, can cooperate actively, and demonstrate good compliance.Patients who have not engaged in any form of regular traditional Chinese health-preserving exercises—defined as at least 30 minutes per session, twice daily, five times per week—during the six months before this trial.Exclusion criteriaPatients younger than 40 years or older than 80 years.Patients diagnosed with COPD who are experiencing an acute exacerbation requiring hospitalization or targeted pharmacological treatment.Patients who have participated in any structured pulmonary rehabilitation program, regular exercise training, or traditional Chinese health exercise programs within the 12 months before screening.Patients with COPD complicated by other respiratory diseases, such as asthma, pulmonary infections, tuberculosis, bronchiectasis, or lung cancer, who are deemed unsuitable for rehabilitation exercises.Patients with COPD complicated by severe diseases in other major systems, including cardiovascular, cerebrovascular, hematologic, hepatic, renal, digestive, endocrine, or nervous systems.Patients unable to cooperate with treatment and assessments due to conditions such as mental disorders or impaired consciousness.Participants concurrently enrolled in other clinical intervention or drug trials.Patients with musculoskeletal disorders or open injuries that preclude limb muscle strength assessment.

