#### Liuzijue Group

Based on the control group, the same standardized medication regimens, as prescribed by clinical respiratory physicians, will be implemented. During this trial, participants will be required to perform regular Liuzijue exercise sessions according to a prescribed regimen. In the two weeks preceding the formal intervention, participants in the Liuzijue group will receive three intensive training sessions conducted by the research team to ensure mastery of the complete movements and key technical elements of the Liuzijue method through systematic instruction. High-definition demonstration videos will be distributed via mobile devices to facilitate correct performance of the prescribed exercises at home, with daily check-ins required. Each participant in the Liuzijue group will be provided with an exercise log card, on which they will record detailed information after each session, including exercise date, time, frequency, duration, location, and perceived exertion (assessed using the Borg CR-10 [Category-Ratio 10] scale, see Table 2). Weekly exercise logs will be submitted at each intensive training session. Simultaneously, researchers will maintain a logbook documenting attendance during the concentrated interventions, collect the exercise log cards, and participants will be engaged in discussions regarding their exercise performance to ensure adherence to this trial’s protocol. During supervised group exercise sessions, trial personnel who have received standardized training will provide on-site correction of participants’ movements. The degree of movement standardization will be systematically documented in the case report forms to ensure consistency of the intervention and to minimize potential impacts on this trial’s outcomes.

**Table 2. T2:** Borg CR-10^a^ rating of perceived exertion scale used to monitor exercise intensity during Liuzijue training sessions. Participants rated their perceived exertion on a scale from 0 ("nothing at all") to 10 ("maximal"), with the target intensity maintained between 4 and 6.

Rating	Description
0	Nothing at all
0.5	Very, very light
1	Very light
2	Light
3	Moderate
4	Somewhat hard
5	Hard
6	Hard
7	Very hard
8	Very hard
9	Very, very hard
10	Maximal

a CR-10: Category-Ratio 10.

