The Liuzijue exercise prescription primarily comprises eight components: the preparatory posture, the “xu” exercise to calm the liver Qi, the “he” exercise to replenish the heart Qi, the “hu” exercise to cultivate the spleen Qi, the “si” exercise to replenish the lung Qi, the “chui” exercise to replenish the kidney Qi, the “xi” exercise to regulate the Sanjiao, and the final position [40]. The Liuzijue exercise is illustrated in Figure 2. Each session lasts approximately 30 minutes and is performed twice daily, five days per week. One day per week is dedicated to supervised, intensive practice at the hospital under the guidance of a rehabilitation therapist, while the remaining six days involve home-based practice using Liuzijue instructional videos. The intervention period lasts 12 weeks.

The intervention will consist of performing two consecutive rounds of the command-version Liuzijue routine issued by the General Administration of Sport of China. All movements will be required to be executed slowly, continuously, smoothly, and with lightness, in precise coordination with the breathing rhythm—inhaling during the upward movement of the upper limbs and exhaling during their descent. The entire practice emphasizes the integration of breath regulation, body posture, and mindful concentration, with participants instructed to maintain relaxed shoulders, a stable core, and natural joint mobility. A single round of Liuzijue requires approximately 15 minutes, resulting in a total intervention duration of about 30 minutes per session. Throughout the practice, attention will be given not only to the accuracy of the movements but also to the synchronization of breathing patterns, thereby maximizing its rehabilitative benefits for the respiratory system.

Participants will be instructed by the research team to take short breaks if they experience fatigue, exhaustion, or dyspnea during exercise, and to resume once symptoms subside. Exercise intensity will be maintained between 4 and 6 on the Borg CR-10 Dyspnea Rating Scale (detailed scoring in Table 2). During exercise sessions, participants’ heart rates will be monitored with the target exercise intensity set at 60%‐80% of each participant’s age-predicted maximum heart rate.

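### The control group's exercise ban is defined at the full Liuzijue dose, so practice below it is not literally barred; the Figure 1 comparator label also leaves out the weekly musculoskeletal care

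*Protocol article*

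**What the plan says.** **Exercise during the trial.** The Control Group section instructs controls to "abstain from any form of regular traditional Chinese health-preserving exercises, defined as twice daily sessions of 30 minutes each, five times per week", and attributes the definition to a previous study. The Liuzijue Group section prescribes sessions of about 30 minutes, two a day, five days a week, for 12 weeks. The Figure 2 caption repeats that dose.

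**Adherence.** Under Compliance Assessment, a Liuzijue participant who completes at least 85% of prescribed sessions has good adherence. For controls, the telephone calls confirm abstention from traditional Chinese health exercise, with no dose given. A control has good adherence if at least 85% of calls are completed and the eligibility criteria are still met. Textbox 1 holds two exercise criteria. The inclusion criterion carries the dose definition and looks back six months. The exclusion criterion carries no dose and looks back 12 months.

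**Comparator.** Controls attend weekly, and the study team will "manage musculoskeletal conditions unrelated to respiratory function (eg, neck, shoulder, low back, and lower limb pain". The section sets limits: "pain treatment will be limited to symptomatic management of common musculoskeletal issues, without any intervention aimed at improving exercise capacity", and no analgesics. The stated purpose is to match contact between the arms. The Figure 1 caption says that patients were allocated "to receive standardized pharmacological treatment alone or combined with a 12-week Liuzijue exercise intervention".

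**The concern.** A rule that keeps controls away from the study intervention should bar that intervention at any dose. Here the word that limits the ban, regular, is defined at the full trial dose, so the instruction as written forbids only practice at the level that the active arm is asked to reach. Controls who practise somewhat less follow the instruction, and the difference between the arms narrows.

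The adherence check does not repair this, because it uses different words. A control who practises three times a week complies with the Control Group section but has not abstained in the sense of Compliance Assessment. Staff who make the calls could classify that person either way. If the per-protocol sensitivity analysis draws on this classification, which the article does not say, its membership would depend on which section was followed.

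The label matters less. A reader of the Figure 1 caption would take the comparator to be drug treatment and nothing else, when the text describes drug treatment with weekly attention visits and symptomatic care.

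**Working it through.** **Inputs**
- Barred exercise (Control Group): 2 sessions a day, 30 minutes each, five times a week.
- Liuzijue prescription (Liuzijue Group; Figure 2 caption): about 30 minutes, 2 a day, 5 days a week, 12 weeks.
- Good-adherence bar, Liuzijue arm (Compliance Assessment): 85% of prescribed sessions.

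**Step 1: compare the ban with the prescription**
- Ban: 2 × 30 × 5 = 300 min/week, or 10 sessions.
- Prescription: 30 × 2 × 5 = 300 min/week, or 10 sessions; over 12 weeks, 10 × 12 = 120 sessions.
- The two are identical.

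**Step 2: what the definition leaves open**

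| Control practice | Min/week | Share of trial dose | Barred as defined? |
|---|---|---|---|
| Once daily, 5 days | 1 × 30 × 5 = 150 | 150/300 = 50% | No |
| Twice daily, 4 days | 2 × 30 × 4 = 240 | 240/300 = 80% | No |
| 9 sessions a week | 9 × 30 = 270 | 270/300 = 90% | No |
| Twice daily, 5 days | 300 | 100% | Yes |

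**Step 3: set this against the adherence bar**
- Bar: 0.85 × 120 = 102 sessions.
- Nine sessions a week: 9 × 12 = 108 sessions; 108/120 = 90%, and 108 exceeds 102.
- The same volume is adherent in the Liuzijue arm and not barred in the control arm.

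This comparison uses the five-day prescription. The Liuzijue Group section also mentions one supervised day plus six home days. On seven days the dose would be 2 × 30 × 7 = 420 min/week (14 sessions), and nine sessions would be 9/14 = 64%, below the 85% bar. The gap in the ban would remain, because anything under 300 min/week would still fall outside it.

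**Step 4: does another section settle the rule?**
- Compliance Assessment asks for abstention with no dose. That is the stricter rule, but it conflicts with the instruction that controls are given.
- Its further condition, that controls still meet the eligibility criteria, leads to Textbox 1. That holds one dosed and one undosed exercise rule, both worded for the period before the trial. It does not say which applies during the 12 weeks.

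**Step 5: the label**
- The caption describes the control condition as drug treatment alone. The Control Group section adds a weekly visit with symptomatic, non-analgesic musculoskeletal care. The caption's description is therefore incomplete, whatever the Liuzijue arm receives.

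**The case against.** The defence of the exercise rule is reasonable. The instruction speaks of any form of regular exercise, and the investigators very likely meant that controls should not practise at all. The telephone check is undosed, at least five calls a week record daily activity, and controls receive no breathing instruction during those calls. Liuzijue guidance is offered to controls only after the trial. Anyone in a traditional exercise programme within 12 months before screening is excluded. Together these make substantial practice by controls unlikely. They do not change what the instruction says, and if the intent was total abstention, stating it costs almost nothing.

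On the label, the Control Group section openly describes the care, its purpose and its limits. In the caption, the word alone can be read as meaning without Liuzijue. The abstract does not use that word: "The control group receives standardized pharmacological treatment, while the Liuzijue group receives the same pharmacological treatment combined with Liuzijue intervention" is a summary that omits the contact matching. Eligibility also removes some of the relevant patients: "Patients with musculoskeletal disorders or open injuries that preclude limb muscle strength assessment". What stands is one imprecise word in a caption, and the need to word the conclusion accordingly.

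Three stronger readings are tempting, and the document does not support them.
- **The Liuzijue arm is denied musculoskeletal care.** For that arm the text says that "the same standardized medication regimens, as prescribed by clinical respiratory physicians, will be implemented" and, of the hospital visit, "One day per week is dedicated to supervised, intensive practice at the hospital under the guidance of a rehabilitation therapist". It neither grants nor rules out symptomatic care, and the section's opening words can be read as building on everything that controls receive. A condensed article's silence is not evidence of a difference.
- **The care goes unrecorded.** Nothing says so. Fields on a case report form are detail that an article commonly omits.
- **The walk-test difference shrinks by a calculable number of metres.** That would need the share of controls who practise and a dose-response relation. The document gives neither.

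**Conclusion.** The point holds as a defect in a stated rule. The control ban equals the full trial dose of 300 min/week, so as defined it does not reach practice of up to nine sessions (270 min) a week, and it does not match the undosed abstention check. The 90% versus 85% comparison rests on the five-day prescription; the gap in the ban does not. Practice by controls would tend to narrow the difference between the arms, but how much would occur, and with what effect, cannot be derived from the document. The contact-matching care is a legitimate, disclosed design choice, and no change to it is called for. The Figure 1 label is a minor secondary correction. Neither part calls the design, sample size or analysis into question.

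**What to change.** **Main change**
1. In Control Group, instruct controls to abstain from any traditional Chinese health exercise, including Liuzijue, at any dose for the duration of the trial. Delete the dose definition there.
2. In Compliance Assessment, use the same definition for control adherence, and state that during the trial it governs in place of the pre-trial exercise criteria in Textbox 1. Without that sentence, the condition that controls still meet the eligibility criteria would keep the ambiguity alive.
3. At the existing control calls, record any minutes of such exercise.
4. Note the date of the change. The 15 controls enrolled at manuscript submission started under the present wording. If the target of 38 is met, 38 − 15 = 23 controls were still to enrol at that point; those who join after the change start under the clear rule.

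**Minor change**

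In the Figure 1 caption, and when the conclusion is written, describe the comparator as standardized medication plus weekly attention visits with symptomatic, non-analgesic musculoskeletal care.

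**Cost**

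An amendment to the wording and one field at calls that already ask about daily activity. The drawbacks are a longer comparator label, a mid-trial change of instruction for controls already enrolled, and reliance on self-reported minutes. No added visits, participants or analyses are needed.

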#### Liuzijue Group

Based on the control group, the same standardized medication regimens, as prescribed by clinical respiratory physicians, will be implemented. During this trial, participants will be required to perform regular Liuzijue exercise sessions according to a prescribed regimen. In the two weeks preceding the formal intervention, participants in the Liuzijue group will receive three intensive training sessions conducted by the research team to ensure mastery of the complete movements and key technical elements of the Liuzijue method through systematic instruction. High-definition demonstration videos will be distributed via mobile devices to facilitate correct performance of the prescribed exercises at home, with daily check-ins required. Each participant in the Liuzijue group will be provided with an exercise log card, on which they will record detailed information after each session, including exercise date, time, frequency, duration, location, and perceived exertion (assessed using the Borg CR-10 [Category-Ratio 10] scale, see Table 2). Weekly exercise logs will be submitted at each intensive training session. Simultaneously, researchers will maintain a logbook documenting attendance during the concentrated interventions, collect the exercise log cards, and participants will be engaged in discussions regarding their exercise performance to ensure adherence to this trial’s protocol. During supervised group exercise sessions, trial personnel who have received standardized training will provide on-site correction of participants’ movements. The degree of movement standardization will be systematically documented in the case report forms to ensure consistency of the intervention and to minimize potential impacts on this trial’s outcomes.

**Table 2. T2:** Borg CR-10^a^ rating of perceived exertion scale used to monitor exercise intensity during Liuzijue training sessions. Participants rated their perceived exertion on a scale from 0 ("nothing at all") to 10 ("maximal"), with the target intensity maintained between 4 and 6.

Rating	Description
0	Nothing at all
0.5	Very, very light
1	Very light
2	Light
3	Moderate
4	Somewhat hard
5	Hard
6	Hard
7	Very hard
8	Very hard
9	Very, very hard
10	Maximal

a CR-10: Category-Ratio 10.

The Liuzijue exercise prescription primarily comprises eight components: the preparatory posture, the “xu” exercise to calm the liver Qi, the “he” exercise to replenish the heart Qi, the “hu” exercise to cultivate the spleen Qi, the “si” exercise to replenish the lung Qi, the “chui” exercise to replenish the kidney Qi, the “xi” exercise to regulate the Sanjiao, and the final position [40]. The Liuzijue exercise is illustrated in Figure 2. Each session lasts approximately 30 minutes and is performed twice daily, five days per week. One day per week is dedicated to supervised, intensive practice at the hospital under the guidance of a rehabilitation therapist, while the remaining six days involve home-based practice using Liuzijue instructional videos. The intervention period lasts 12 weeks.

The intervention will consist of performing two consecutive rounds of the command-version Liuzijue routine issued by the General Administration of Sport of China. All movements will be required to be executed slowly, continuously, smoothly, and with lightness, in precise coordination with the breathing rhythm—inhaling during the upward movement of the upper limbs and exhaling during their descent. The entire practice emphasizes the integration of breath regulation, body posture, and mindful concentration, with participants instructed to maintain relaxed shoulders, a stable core, and natural joint mobility. A single round of Liuzijue requires approximately 15 minutes, resulting in a total intervention duration of about 30 minutes per session. Throughout the practice, attention will be given not only to the accuracy of the movements but also to the synchronization of breathing patterns, thereby maximizing its rehabilitative benefits for the respiratory system.

Participants will be instructed by the research team to take short breaks if they experience fatigue, exhaustion, or dyspnea during exercise, and to resume once symptoms subside. Exercise intensity will be maintained between 4 and 6 on the Borg CR-10 Dyspnea Rating Scale (detailed scoring in Table 2). During exercise sessions, participants’ heart rates will be monitored with the target exercise intensity set at 60%‐80% of each participant’s age-predicted maximum heart rate.

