### Randomization and Blinding

SPSS (version 27.0; IBM) will be used to generate a random number list. A block randomization algorithm will assign a unique random number to each participant, and this information will be kept strictly confidential. All random numbers will be sealed in opaque envelopes, and group allocation will be performed using the envelope method. After completing baseline assessments, trained researchers will randomly select envelopes to assign participants to either the control group or the Liuzijue group according to the numbers contained therein.

Given that this trial involves physical intervention, it is difficult to blind the participants. Therefore, independent outcome assessors who are not involved in participant recruitment, intervention delivery, or group allocation will be used. All outcome assessments will be conducted by these blinded assessors according to standardized procedures. In addition, data analysts will also be blinded to group allocation in order to minimize bias and enhance the reliability of the results.

If it becomes necessary to unblind the outcome assessors or data analysts, the reasons must be documented and reported in detail. During data analysis, appropriate statistical methods will be applied to control potential bias.

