9	Multifidus	The junction between the middle $\frac{1}{3}$ and medial $\frac{1}{3}$ of the line from PSIS^d^ to L5^e^

a SENIAM: Surface Electromyography for the Non-Invasive Assessment of Muscles.

b C7: the seventh cervical vertebra.

c ASIS: anterior superior iliac spine.

d PSIS: posterior superior iliac spine.

e L5: the fifth lumbar vertebra.

The sEMG assessment will consist of static and dynamic tests. In the static test, participants will stand quietly while EMG signals are recorded for 5 seconds at rest, at the end of maximal inspiration, and at the end of maximal expiration, with each condition repeated three times at two-minute intervals. The dynamic test will involve a 10-meter walking trial, during which participants are instructed to walk as fast as possible along a corridor while both walking time and EMG signals are recorded simultaneously. The electrode placement for sEMG is illustrated in Figure 3. The sEMG data will be collected in week 0 and week 13.

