#### 6MWT

6MWT is a widely used method for evaluating exercise capacity in patients with respiratory disorders and for assessing the efficacy of clinical interventions. Previous studies [48,49] have demonstrated that the 6MWT serves as a valid and reliable measure of functional capacity and health-related quality of life in patients with COPD, while also providing an indicator of disease severity. Based on previous findings [37,38], the MCID for 6MWT ranges from 30 to 54 m, and the baseline SD is between 70 and 90 m. This study will use a 6MWT data acquisition system in combination with a dynamic vital signs monitor, CB200 (Contec), for testing. Participants will be instructed to walk back and forth along a 30-meter flat corridor at their maximum tolerable speed for six minutes. Distance markers will be placed every 5 meters to aid measurement. The recording device will capture the total walking distance as well as heart rate and oxygen saturation before and after the test. The 6MWT outcome will serve as a primary indicator of intervention efficacy, assessed in week 0 and week 13.

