#### PFT

PFT is widely recognized as the gold standard for the diagnosis and clinical efficacy assessment of COPD. A previous study [50] has demonstrated that PFT not only provides precise measurements of multiple pulmonary function parameters at rest but also serves as a reliable predictor of long-term prognosis. In this study, PFT will be performed by experienced respiratory technicians in the Pulmonary Function Laboratory of Shanghai Changhai Hospital using a Masterscreen-PFT system (Jaeger), strictly following the standardized procedures recommended by the 2021 ATS/ERS guidelines [51]. Before testing, participants will inhale salbutamol, and measurements will be conducted 25 minutes postinhalation [52]. During testing, participants will be instructed to perform forced exhalations lasting at least six seconds per maneuver, followed by brief rest intervals, and to repeat the maneuver until at least three acceptable measurements are obtained. Recorded parameters include FVC, FEV1, the FEV1-to-FVC ratio (FEV1/FVC), percentage of predicted FEV1 (forced expiratory volume in one second percentage predicted), percentage of predicted FVC (forced vital capacity percentage predicted), and the percentage value of FEV1/FVC (FEV1/forced vital capacity percentage). PFT assessments will be performed in week 1 and week 13.

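### The baseline PFT week and the Liuzijue training window do not fit the trial's own schedule of allocation and baseline tests

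*Protocol article*

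**What the plan says.** Table 1 sets the time axis as "Time point (week) -2 0 1‐12 13", with columns for baseline, allocation, intervention and assessment. The row "Randomization and allocation" is ticked at week 0 only. PFT, 6MWT, SGRQ, sEMG, IKMT and kinematics are each ticked at week 0 and week 13. A row named "Centralized guidance" is ticked at week -2 only and is not defined anywhere in the article. No row shows Liuzijue training after allocation.

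Randomization and Blinding fixes the order: "After completing baseline assessments, trained researchers will randomly select envelopes to assign participants".

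The Liuzijue Group section places training as follows: "In the two weeks preceding the formal intervention, participants in the Liuzijue group will receive three intensive training sessions conducted by the research team".

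The outcome sections date the coprimary measures in line with Table 1: "The sEMG data will be collected in week 0 and week 13", and "The 6MWT outcome will serve as a primary indicator of intervention efficacy, assessed in week 0 and week 13". SGRQ, IKMT, and gait and plantar pressure also carry weeks 0 and 13. The PFT section alone differs: "PFT assessments will be performed in week 1 and week 13".

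Statistical Analysis names a linear mixed model for the primary outcomes and, where appropriate, ANCOVA adjusted for baseline for continuous secondary outcomes. PFT is listed among the secondary outcomes.

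**The concern.** A baseline value should be taken before allocation, so that neither treatment nor knowledge of the group can affect it. Two instructions put that at risk.

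For PFT, a laboratory that follows the PFT section would take the first measurement in an intervention week. That value would come after randomisation. In the Liuzijue arm it would also come after the training sessions and possibly after exercise had begun. Using it as the ANCOVA covariate adjusts for something that treatment may already have changed, and any early effect would be partly adjusted away.

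For training, the sessions are tied to a two-week period that cannot lie wholly between allocation and the start of the intervention. Staff who meet both instructions must bend one of them, and the article does not say which. If the two-week period is kept and the group becomes known early, the week-0 6MWT and sEMG baselines would follow training in one arm only. If the order in Randomization and Blinding is kept, those baselines are unaffected and the training period has to change.

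**Working it through.** No sample size or power figure is involved. The check sets the stated times side by side.

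**Inputs**

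| Item | Stated time | Place |
|---|---|---|
| Screening, consent, centralized guidance | week -2 | Table 1 |
| Allocation | week 0 | Table 1 |
| Baseline tests, including PFT | week 0 | Table 1 |
| Baseline tests relative to envelope | before | Randomization and Blinding |
| First sEMG, 6MWT, SGRQ, IKMT, gait and plantar pressure | week 0 | each outcome section |
| First PFT | week 1 | PFT section |
| Liuzijue training | the two weeks before the intervention | Liuzijue Group |
| Intervention | weeks 1 to 12 | Table 1 |

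**Check 1: PFT.**
- Difference between text and table: 1 − 0 = 1 week.
- Week 1 lies in the intervention period (1 to 12) and after allocation (week 0).
- The PFT section therefore disagrees with Table 1 on the week, and with Randomization and Blinding on the order.
- Up to one of the 12 intervention weeks could precede the value used as baseline. This is an upper bound, since week 1 may mean its first day.

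**Check 2: training window.**
- Start of intervention: week 1.
- Start of the two-week window: 1 − 2 = week -1, so the window covers weeks -1 and 0.
- Time from allocation to start of intervention: 1 − 0 = at most about 1 week.
- Part of the window before any Liuzijue group exists: at least about 2 − 1 = 1 week. How much more depends on the day in week 0 on which the envelope is opened.

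**What follows under each reading**

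- *Baseline tests, then envelope, then training.* The 6MWT and sEMG baselines are pre-allocation and so precede training. The only fault is that a two-week period does not fit into about one week.
- *Two-week period kept, with the group known before week 0.* Training could then precede the week-0 6MWT and sEMG in one arm. This breaks the order in Randomization and Blinding.

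For PFT neither reading helps: a week-1 value is post-randomisation under both.

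**The case against.** The strongest reply is that the order is already fixed where it matters most. Randomization and Blinding puts baseline tests before the envelope, and the 6MWT and sEMG sections and Table 1 date those tests to week 0. Training is described for members of the Liuzijue group, and there are none until the envelope is opened. Nowhere does the article say that training precedes allocation. This stands, and it confines the second fault to a window that does not fit.

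A reader might go further and infer that controls are taught Liuzijue at week -2, taking the centralized guidance row to be the training. The documents do not support that. The row is undefined and sits under enrollment, beside consent and history. The Liuzijue Group section gives training to that group, and the Control Group section excludes respiratory exercise instruction from control contacts and defers Liuzijue guidance until after the trial. The row needs a definition, but it is not evidence of contamination.

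A reader might also want to convert early exposure into lost metres of 6MWT and lost power. The documents give no basis for the fraction of effect that three sessions would produce, and the loss would arise only if the stated order were broken.

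Finally, week 1 for PFT may be a slip, since every other outcome says week 0, and PFT is a secondary outcome. That is plausible and limits the reach of the fault. It does not remove it, because the sentence is an instruction that someone may follow.

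**Conclusion.** Two timing contradictions hold.

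1. The first PFT is dated one week later in its own section than in Table 1, inside the intervention period and against the stated order of baseline tests and allocation. If followed, the baseline covariate for a secondary outcome is post-randomisation and, in the Liuzijue arm, post-training. This rests on the text alone.
2. The two-week training window cannot lie between week-0 allocation and a week-1 start. At most about one week is available.

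The conclusion does not extend to the coprimary baselines unless the order in Randomization and Blinding is not kept in practice, and the article gives no sign of that. The post-randomisation covariate problem reaches PFT only: the primary outcomes use a mixed model, and the other secondary measures are dated week 0. No size can be put on bias or loss of power for 6MWT or sEMG. For PFT the direction of concern is clear, but its size is unknown.

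The point should be settled now because recruitment is under way. A missed pre-allocation baseline cannot be recovered, and 76 − 23 = 53 of the planned participants had still to be enrolled at submission.

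**What to change.** - Correct the PFT section to week 0, before allocation, in agreement with Table 1 and Randomization and Blinding.
- Reconcile Table 1, Randomization and Blinding, and the Liuzijue Group section into one sequence: all baseline measures completed, then the envelope opened, then Liuzijue training. Add the training as a row in Table 1 after allocation. The investigators should decide how its length fits the start of the intervention.
- State what centralized guidance at week -2 contains and who receives it.
- For the 23 participants already enrolled (15 control, 8 Liuzijue), check the dates of each baseline test, of allocation and, in the Liuzijue arm, of the first training session. Flag any baseline taken after allocation or exposure. For PFT, add a sensitivity analysis excluding the flagged values, alongside the main analysis of all randomised participants.

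The cost is schedule wording and a date check on 23 records, with no added visits. There is one real downside: placing training after allocation may require a small adjustment to the training window or to the gap between baseline and the start of the intervention.
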